#### 2.10.3. Prevalence of DB in Patients with NSCNP

As there are no established reference standards for DB [33], the diagnostic accuracy of respiratory measurements relating to DB in patients with NSCNP cannot be examined. Instead, as previously proposed [42], the prevalence of DB in patients with NSCNP can be presented, using cut-off scores established from previous studies performed in an asymptomatic population without a respiratory condition (ETCO_2_ with a cut-off score of 35 mm Hg, the NQ with a cut-off score of 19), and the Hi-Lo test, for the determination of the type of breathing, as single or combined (in pairs, or using all three) outcomes, to identify the percentage of the population with NSCNP that exhibits respiratory dysfunction. 

### 2.11. Biomechanical Outcomes Reliability Investigation in Patients with NSCNP

#### Reliability of Cervical ROM and FHP

As novel measurement methods will be used to measure cervical ROM and CVA, the reliability of both proposed cervical ROM measurement methods will be separately evaluated, and parallel forms reliability between the two methods will be tested in a proportion of this population. Additionally, CVA reliability will be measured, and this will be conducted with a new smartphone-based application. All test-retest reliability measurements will be performed by a single examiner on the same day of initial assessment, with adequate times between measurements (Figure 3). All reliability assessments will be performed in the first 35–40 participants of the main trial to assess their reliability level. Pre-post comparisons of any of these measurements that prove not to be sufficiently reliable will not be further considered. 

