### 2.7. Participants’ Characteristics

At least 90 adult volunteers of both genders, aged between 25 and 65 years, and with mechanical chronic neck pain (for more than 12 weeks), Grade I or II according to the Task Force on Neck Pain classification (Nordin 2009) [22], negative Spurling’s test, traction test, upper limb tension test, and shoulder abduction test, understanding and fluently speaking the Greek language, and the absence of another serious pathology, will be included in the present study. The diagnosis of non-specific mechanical chronic neck pain will be performed after history taking and physical examination (according to the clinical protocols of IFOMPT) [23] and medical X-rays, according to the Canadian Cervical Spine Rule (C-Spine) and the National Emergency X-Radiography Utilization Study (NEXUS) [24]. Patients will also be selected on the basis of demonstrating DB in at least one of a series of tests conducted to assess the extent of their DB (biomechanical, biochemical, psychological).

The following criteria will be used to determine who is excluded: history of cervical trauma, whiplash injury, or cervical surgery; cervical hernia; spinal degenerative disease; upper limb pain radiation; having received physiotherapeutic treatment for the cervical region within the previous three months; metabolic bone diseases and osteoporosis; cardiac or respiratory insufficiency; pregnancy; neoplasm; infectious diseases; psychological diseases; red flags (overnight pain, serious muscle spasm, weight-loss unrelated to diet, daily headache, dyspnea, confusion, and loss of consciousness); recent consumption of analgesics, anti-inflammatories, or muscle relaxants; systemic illnesses; and fibromyalgia.

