### 2.9. Outcomes

The evaluations will take place at all time-points: before the treatment sessions (week 0), after ten treatment sessions (week 4), and four months after the beginning of the trial (week 16). The primary outcomes will be: functional disability (NDI) [25] and pain (VAS) [26]. Several secondary outcomes will also be evaluated: cervical range of motion (CROM) [27], craniovertebral angle (CVA) [28], Nijmegen Questionnaire (NQ) [29,30], Hi-Lo test [31], breath holding time (BHT) [32,33], single breath count (SBC) [34], end tidal CO_2_ (ETCO_2_) [35] and respiratory rate (RR) [36], chest wall expansion (CWE) [37], the Hospital and Anxiety Depression Scale (HADS) [38], the Tampa Scale for Kinesiophobia (TSK) [39] and adverse events [40]. All outcomes are briefly presented below. The corresponding references for each of the above outcomes include reliability and validity details, except for some further testing proposed in Section 2.10 and Section 2.11.

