#### 2.9.2. Secondary Outcome Measures

Range of motion (ROM) [27]: A smartphone-based application (iHandy Level: https://play.google.com/store/apps/details?id=com.ihandysoft.carpenter.level.free&hl=et&gl=US (accessed on 10 May 2022)) downloaded to a smartphone (Model P30/ELE-L29, Huawei Smartphone, China 2019, purchased January 2021), in parallel with a sensor-based commercially available device (KFORCE SENS electronic goniometer, KINVENT-France), will be used to accurately measure ROM during neck movements of flexion-extension, left-right side flexion, and left-right rotation. 

Craniovertebral Angle (CVA) [28]: Lateral photography examination of the FHP through lateral photographs can provide very reliable estimates. FHP will be estimated in a relaxed sitting position for all participants. A smartphone-based application (Forward Head Posture-FHP app), available on Google Play (https://play.google.com/store/apps/details?id=com.ysjworld.fhp&hl=en&gl=US (accessed on 10 May 2022)), will be used for CVA angle measurements.

Nijmegen Questionnaire (NQ) (Greek version 2014) [29]: Screening tool used to detect patients with hyperventilation complaints and DB patterns. Scores > 19 are used as the cut-off score to separate hyperventilatory patients from normal subjects [30]. NQ values in healthy individuals range from 10 to 12 ± 7, and values have been observed to decrease towards these levels in subjects with DB after breathing retraining [30].

Hi-Lo test [31]: The examiner will be given instructions on how to conduct and record results from the Hi-Lo test, including the following: “Examiner at the front and slightly to the side of the individual has to place one hand on the patient’s sternum and the other hand on their upper belly. The examiner must evaluate if and to what extent abdominal or thoracic motion predominates while breathing. Additionally, paradoxical breathing needs to be considered, as well as the degree of abdominal or thoracic breathing rate.” This test evaluates DB.

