### 2.14. Sample Size Calculation

The estimation of the sample size was performed with the use of the G*Power, version 3.1 program. For a three parallel groups design involving three repeated measures (pre, post-treatment, and one follow-up), in order to achieve a statistical power of 0.80 in detecting a medium effect size (Cohen’s f = 0.25) in the interaction effect, at a significance level of 5% (0.05), it was calculated that a minimum sample size of 80 individuals would be required. Taking into consideration a dropout rate of 10%, it was estimated that 30 individuals per group would need to be initially recruited [21].

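### Agreement between the two range-of-motion devices is restricted to the first 35–40 participants, although on the plain reading all of about 90 supply the paired baseline readings

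*Protocol article*

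**What the plan says.** All references are to the protocol article.

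- **Section 2.9.2 (ROM)** names a smartphone application which, "in parallel with a sensor-based commercially available device (KFORCE SENS electronic goniometer, KINVENT-France), will be used to accurately measure ROM during neck movements". Neither device is limited to some of the participants.
- **Section 2.9** lists cervical ROM as a secondary outcome and sets the schedule: "The evaluations will take place at all time-points: before the treatment sessions (week 0"), followed by weeks 4 and 16.
- **Section 2.11** plans test-retest reliability for each ROM method and for the craniovertebral angle. For the comparison of the two ROM methods it states that "parallel forms reliability between the two methods will be tested in a proportion of this population". It then fixes the sample for everything under that heading: "All reliability assessments will be performed in the first 35–40 participants of the main trial". It adds that pre-post comparisons of measurements found insufficiently reliable will be dropped.
- **Sections 2.7 and 2.14** give the trial size: "At least 90 adult volunteers of both genders", and "it was estimated that 30 individuals per group would need to be initially recruited".
- **Objectives of the Proposed Study** lists the reliability of the biomechanical assessments as objective 4.

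**The concern.** Section 2.11 puts two different questions under one sample restriction. Test-retest reliability needs extra repeat measurements, so confining it to a subset is a sensible economy. Agreement between two devices needs only one reading from each device in the same person. If both devices are used in everyone, as 2.9.2 reads, those pairs exist for the whole trial and the restriction saves no measurement.

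What is at stake is the precision with which objective 4 is answered for ROM. The result may also carry some weight in the trial itself, because 2.11 uses reliability to decide whether a measurement's pre-post comparisons are kept. The article does not say whether between-device agreement, as opposed to test-retest reliability, feeds that decision. The primary outcomes (neck disability and pain) are not affected.

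**Working it through.** **Inputs from the article.** Subset: 35–40 (2.11). Trial size: at least 90, or 30 per group (2.7, 2.14). The article gives no expected reliability coefficient, so 0.70, 0.80 and 0.90 below are assumptions chosen to show a range.

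**1. The plan's own recruitment figure.** Section 2.14 says "it was calculated that a minimum sample size of 80 individuals would be required" and then allows for dropout ("Taking into consideration a dropout rate of 10" per cent). 80 / 0.90 = 88.9, so 89, which becomes 90 for three equal groups. The denominator of 90 is reproduced. The 35–40 has no stated derivation.

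**2. Share of baseline pairs left out.**
- n = 35: 1 − 35/90 = 61%, or 55 pairs.
- n = 40: 1 − 40/90 = 56%, or 50 pairs.

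**3. Precision of a two-method consistency intraclass correlation (ICC).** With F0 = (1 + ICC)/(1 − ICC) and q the 97.5% point of F on (n − 1, n − 1) degrees of freedom, the limits are (F0/q − 1)/(F0/q + 1) and (F0·q − 1)/(F0·q + 1). The values of q are 1.981 (n = 35), 1.891 (n = 40) and 1.519 (n = 90).

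Worked case, ICC 0.80, so F0 = 9:
- n = 35: F0/q = 4.543 and F0·q = 17.830, giving 0.639 to 0.894.
- n = 40: 4.760 and 17.016, giving 0.653 to 0.889.
- n = 90: 5.924 and 13.673, giving 0.711 to 0.864.

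| Assumed ICC | n = 35 | n = 40 | n = 90 | Interval narrower at 90 than at 40 / 35 |
|---|---|---|---|---|
| 0.70 | 0.48–0.84 | 0.50–0.83 | 0.58–0.79 | 35% / 39% |
| 0.80 | 0.64–0.89 | 0.65–0.89 | 0.71–0.86 | 35% / 40% |
| 0.90 | 0.81–0.95 | 0.82–0.95 | 0.85–0.93 | 36% / 41% |

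For 0.80 the widths are 0.255, 0.236 and 0.153: 1 − 0.153/0.255 = 40% and 1 − 0.153/0.236 = 35%.

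**4. Precision of the limits of agreement.** The half-width of the 95% interval for each limit, in standard deviations of the between-device difference, is t·√(1/n + 1.96²/(2(n − 1))). This gives 0.59 (n = 35), 0.55 (n = 40) and 0.36 (n = 90), a reduction of 39% or 35%. It does not depend on the assumed ICC.

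**5. Does the restriction save anything?** Under 2.9 and 2.9.2 read plainly, the week-0 pair is part of the ordinary outcome assessment for every participant. Extending the agreement analysis to all of them then adds no measurement.

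**The case against.** **Nothing is wrong with 35–40.** Section 2.11 makes a consistent choice, and a sample of that size gives a workable estimate. This stands. The loss is one of precision in a secondary objective, and the gain is ordinary sample-size arithmetic. No reliability threshold is stated, so no decision can be shown to change.

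**Use of both devices in everyone is inferred.** Also correct: no single sentence says it. Restricting the comparison to a proportion of participants could mean that the second device is used only there, and Figure 3, which gives the order of assessments, is not shown. The plain wording of 2.9 and 2.9.2 still favours parallel use throughout. If that is not intended, the two sections need reconciling.

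**An early subset serves the keep-or-drop rule.** It may, and it puts test-retest and between-device results on the same people. But the rule acts on pre-post comparisons, which come later, so an early look does not prevent a final estimate from all pairs.

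**This is detail for the full protocol.** The point is not an omission: the article positively fixes the subset for all reliability assessments.

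Two stronger readings are tempting and are not supported:

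- A reader might infer that more than half the paired readings are thrown away. They remain ROM outcome data and are outside only the agreement analysis.
- A reader might infer that the earliest participants are unrepresentative because the examiner is still learning. Section 2.11 calls the methods novel, but nothing says the examiner is inexperienced with them. Section 2.8 specifies a physiotherapist with at least six years of clinical practice, and 2.6 has recruitment consecutive. A learning effect would in any case bear on the test-retest results from the same people.

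**Conclusion.** The point holds as a minor one. On the plain reading of 2.9 and 2.9.2, section 2.11 leaves 50–55 of about 90 baseline device pairs (56–61%) out of the agreement analysis for objective 4, without a stated reason. The subset estimate is valid but less precise than it need be: using all baseline pairs would narrow the interval by roughly 35–40%.

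This rests on two assumptions: that both devices are used in all participants at week 0, and, for the ICC intervals, that the coefficient lies in the 0.70–0.90 range shown. If the first fails, the precision gain disappears and what remains is a wording conflict between 2.9.2 and 2.11.

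**What to change.** In 2.11, keep the first 35–40 participants for the test-retest measurements and for any early look at reliability. State that the final between-device agreement for ROM will be computed from all participants with both week-0 readings (about 90).

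If the second device is intended only for the subset, leave 2.11 as it is and amend 2.9.2 to say so.

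Cost: one sentence in either case. On the plain reading the first option needs no additional measurements, because the pairs are already part of the baseline assessment.

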### 2.12. Interventions

Ten treatment sessions will be administered to all participants, thrice for the first two weeks and twice for the third and fourth weeks, lasting for 40 min per session. The sessions will be individually administered in a reserved room with adequate lighting, music, and air conditioning. 

The manual therapy program will be applied by a physical therapist (main researcher), a clinical instructor of manual therapy, PhD candidate, with an OMT diploma from a recognized IFOMPT program, certified as Mulligan Practitioner, with two Master of Science degrees from the Athens Medical School, Greece, and 20 years of experience in clinical practice. A physical therapist with a Master of Science degree from the Athens Medical School and 17 years of experience in clinical practice will administer the traditional physiotherapy program (Group C) and the sham diaphragmatic manual therapy component (Group B). Sham diaphragmatic manual therapy will be administered via a therapeutic ultrasound device [43]. 

The participants can only receive the assigned treatment. They will be advised against combining the treatment they were allocated to with medication or other physical therapy approaches. Any deviation from the treatment sessions administration (missing more than one appointment) or any worsening of symptoms will be reasons for exclusion. The interventions proposed for each group are described briefly below, and in detail in the Supplementary Materials. All selected interventions are widely applied in the field of physical therapy and are safe when administered by appropriately trained physical therapists. 

**Group A:** This group will receive CMT [44,45,46,47], DMT [48,49,50], and BREx [51,52]. Initially, cervical manual therapy (CMT) will be applied for 20 min, consisting of cervical spine inter-vertebral mobilization techniques, according to the Mulligan Concept, and soft tissue techniques. Subsequently, in order to indirectly stretch and mobilize the fibers of the diaphragm, diaphragmatic manual therapy will be used, which should result in improved muscle contraction and reduced tension. The doming diaphragmatic technique and the manual diaphragmatic release technique, both as described by Leon Chaitow, will be among the experimental techniques employed. For 10 min, both maneuvers will be performed in 2 sets of 10 repetitions each, separated by 1 min. Finally, breathing reeducation exercises, according to the Papworth method, will be implemented for 10 min, consisting of: (i) recognition of the abnormal breathing pattern, and practicing stomach and nose breathing retraining, (ii) slow breathing and controlled breath holding, (iii) relaxation techniques training, (iv) progressing breathing retraining in everyday life, with emphasis on postural correction, and (v) breathing reeducation exercises for home use, with the help of a booklet and videos, with emphasis on postural correction and with the instruction to practice these at least once per day. 

**Group B:** This group will receive CMT/soft tissue therapeutic techniques, plus sham DMT. Initially, the same manual therapy for the cervical spine (according to the Mulligan Concept and soft tissue techniques) as that used in Experimental Group A will be administered for 20 min. Additionally, sham DMT will be applied via therapeutic ultrasound (Sonopuls 692 Enraf-Nonius) sham administration in the sitting position for 10 min [38]. The equipment will be switched on, but the intensity will not be raised (0 W/cm^2^); therefore, the equipment will appear working, but no therapeutic dosage will be administered. The same therapist will carry out all the sham ultrasound techniques. Moreover, for 10 min, guidelines for activities of daily living (housekeeping: cleaning, sweeping) will also be provided, with emphasis on postural correction.

**Group C:** This group will receive a typical conventional physiotherapy program, therefore acting as an active control group for this trial. Initially, Transcutaneous Electric Nerve Stimulation (TENS) will be applied, with a pulse duration of 250 microseconds at a frequency of 80 Hz for 15 min in the suboccipital region and the trapezius bilaterally. Then, Pulsed Microwave Diathermy (Enraf-Nonius RADARMED 950+), will be applied in the sitting position, for 10 min. Soft tissue techniques (deep soft tissue massage) will be applied at a slow speed for 15 min. Massage therapy, included gliding and kneading techniques will be applied over the trapezius (upper, lower, and middle fibers), splenius capitis, and levator scapulae muscles [53].

At the end of the interventions, leaflets will be given to the participants of Group B and Group C, describing general stretching exercises for the cervical spine.

Further details of the techniques applied are provided in the Supplementary Materials. However, leaflets with intervention details will be provided to participants of all groups to enhance adherence to the program, as the exercises will also be performed by participants at home. 

At the end of the trial, subjects will be asked which group they thought they were allocated in, to determine any potential bias.

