### 2.5. Randomization and Blinding Procedures

After the initial evaluation, random allocation of participants into the trial groups will be performed. The block randomization method will be employed, using blocks of three participants, for their distribution into the following groups: Experimental Group A: Diaphragmatic Manual Therapy (DMT) plus Cervical Manual Therapy (CMT) plus Breathing Reeducation Exercises (BREx); Experimental Group B: Cervical Manual Therapy plus sham Diaphragmatic Manual techniques; or Control Group C: Conventional Physiotherapy (CP) program. Subjects will be divided into three groups by means of balanced randomization, carried out with specialized software (http://www.randomizer.org/ (accessed on 10 May 2022)). 

Individuals will be assigned in a covert manner, using sealed, sequentially numbered opaque envelopes [21]. An impartial researcher, who is not involved in the recruitment, assessment, or intervention process, will carry out the randomization and concealed allocation. The researcher in charge of carrying out the treatment programs will only open the envelopes at the time of intervention.

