Breath Holding Time (BHT) [32]: This test is an indicator of a person’s respiratory response to biochemical, biomechanical, and psychological factors, and it seems that abnormally shortened BHT may indicate abnormalities in respiratory function that are closely related to DB. Participants will be instructed to assume a comfortable sitting position and breathe normally and gently, in and out, and at the end of a normal exhalation, they will be asked to pinch their nose and hold their breath. The instruction is to hold their breath to the point when they cannot hold their breath any longer and are required to breathe in again. According to Kiesel (2020) [33], a BHT < 25 s is considered as a sign of DB.

Single Breath Count (SBC) [34]: Participants will be requested to count out loud after maximal inspiration. The ability to reach a count of 50 (corresponding to 25”) is considered as normal respiratory function. This test evaluates DB.

End-Tidal CO_2_ (ETCO_2_) [35] and Respiratory Rate (RR) [36]: These outcomes are measured by a standard capnograph unit. An ETCO_2_ average value that is less than 35 mm Hg over a 12 min period and an average RR of more than 16 breaths/min, will be considered as signs of DB.

Chest Wall Expansion (CWE) [37]: A tape measure will be used to determine the difference between the readings of thoracic cage circumference acquired during deep inspiration and expiration, with higher values indicating a better result.

Hospital and Anxiety Depression Scale (HADS) (Greek version 2008) [38]: Anxiety and depression are measured by the anxiety and depression level assessment scale commonly used in musculoskeletal research, with 7 items contained in each of the subscales (range of scores between 0–21 for each), assessing the two constructs. For each of the two subscales, a score of >8 denotes clinically relevant anxiety/depression.

Tampa Scale for Kinesiophobia (TSK) (Greek version 2005) [39]: Kinesiophobia is a frequently utilized psychological measurement of pain-related fear in musculoskeletal clinical conditions. The translated version of the original 17-item questionnaire will be used.

Adverse events [40]: Potential adverse effects of therapy will be evaluated during and after the physiotherapy treatment, according to a proposed 5-level rating. Should any patient present with serious adverse events, they will be withdrawn from the trial and referred back to their doctor for further evaluation.

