### 2.15. Statistical Analysis

Baseline characteristics and all outcome measurements will be analyzed initially in each group for normality of their distribution using the Shapiro–Wilk Test. Descriptive statistics will be used to present the distribution of the data.

Statistical analysis for the RCT will be conducted, based on intention-to-treat analysis. In this way, the individuals will be analyzed in the groups in which they were randomly allocated. A separate analysis will be conducted in case any protocol deviations occur for part of the population, such as low adherence with the organized treatment sessions, low home compliance (<50% attendance), or should patients withdraw themselves from the RCT. Linear mixed models (two-way mixed ANOVA) with one repeated measures factor (time) and another between-groups factor (group), especially considering the interaction between the factors of time (week 0, week 4, and week 16) and group (A and B, A and C, B and C). Additionally, post hoc tests will be employed to determine the source of the interaction, if significant. 

The principal components analysis method will be performed for the factor analysis of the NQ. Pearson’s bivariate correlations will be employed for the examination of concurrent validity of respiratory outcomes.

For all analyses, a significance level of 5% will be considered. All data processing will be performed using the IBM SPSS software, version 28. 

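### Exclusion after randomisation for missed sessions or worsening symptoms is not reconciled with the intention-to-treat analysis, and the article does not say that excluded patients are still followed up

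*Protocol article*

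**What the plan says.** Section 2.5 places allocation before treatment: "After the initial evaluation, random allocation of participants into the trial groups will be performed". Section 2.12 sets the treatment course: "Ten treatment sessions will be administered to all participants, thrice for the first two weeks and twice for the third and fourth weeks". The same section then gives the rule at issue: "Any deviation from the treatment sessions administration (missing more than one appointment) or any worsening of symptoms will be reasons for exclusion". It does not define worsening, name who judges it, or say what the patient is excluded from.

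Section 2.9.2 says of patients with serious adverse events that "they will be withdrawn from the trial and referred back to their doctor".

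Section 2.15 states the analysis principle: "Statistical analysis for the RCT will be conducted, based on intention-to-treat analysis". It explains that "the individuals will be analyzed in the groups in which they were randomly allocated", and adds: "A separate analysis will be conducted in case any protocol deviations occur for part of the population, such as low adherence". Low home compliance and self-withdrawal are the other examples it gives. Section 4 lists intention-to-treat among the grounds for expecting high internal validity.

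**The concern.** An intention-to-treat comparison needs outcome data from everyone randomised, whatever happened during treatment. Section 2.12 can be followed in a way that stops those data being collected. A patient who misses a second appointment is excluded under Section 2.12, but under Section 2.15 belongs to the randomised group and also to a separate low-adherence analysis.

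The worsening criterion matters more. The primary outcomes are the Neck Disability Index (NDI) and pain on the visual analogue scale (VAS) (Section 2.9), so worsening symptoms in a neck-pain trial will usually be worsening on what these scales measure. Removing patients on that ground selects on something close to the outcome. If the arms differ in how many patients worsen, or in how readily worsening is acted on, the remaining groups are no longer comparable. Week 4 and week 16 scores that were never collected cannot be recovered by a later analysis plan.

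**Working it through.** **1. The sections side by side**

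- Missing two or more sessions: excluded (2.12); analysed as allocated, with a separate analysis for low adherence (2.15).
- Worsening of symptoms: excluded (2.12); not mentioned in 2.15 beyond the general rule that patients are analysed as allocated.
- Serious adverse event: withdrawn from the trial (2.9.2); again only the general rule in 2.15.
- Measurement at weeks 4 and 16 after any of these events: not stated in any section.

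Eligibility exclusions are listed separately in Section 2.7, so the Section 2.12 rule is not a baseline criterion.

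**2. The plan's own figures**

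Sessions: 3 + 3 + 2 + 2 = 10, as stated. Recruitment (Section 2.14): 80 / (1 − 0.10) = 88.9, so 89, rounded up to 30 per group, or 90. This reproduces. The margin over the stated minimum is 90 − 80 = 10 patients.

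**3. Attendance rule (illustrative)**

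The documents give no missed-session rate. Assume each session is missed independently with probability p, with no rebooking, and that exclusion removes outcome data.

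P(miss 2 or more of 10) = 1 − (1 − p)^10 − 10p(1 − p)^9

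- p = 0.02: 1 − 0.817 − 0.167 = 0.016, about 1.5 of 90 excluded.
- p = 0.05: 1 − 0.599 − 0.315 = 0.086, about 7.8 of 90 excluded, 82 left.
- p = 0.10: 1 − 0.349 − 0.387 = 0.264, about 23.8 of 90 excluded, 66 left.

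The 10% allowance is passed between 5% and 10% missed sessions, before ordinary dropout or worsening is counted.

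**4. Worsening rule (illustrative)**

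The documents give no worsening rate. Assume improvement is normal with mean μ and SD 1, and that everyone with improvement below 0 is removed entirely. The fraction removed is 1 − Φ(μ), and the mean of those left is μ + φ(μ)/Φ(μ).

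- μ = 1.5: 6.7% removed; mean 1.5 + 0.1295/0.9332 = 1.639.
- μ = 1.0: 15.9% removed; mean 1.0 + 0.2420/0.8413 = 1.288.
- μ = 0.5: 30.9% removed; mean 0.5 + 0.3521/0.6915 = 1.009.

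Two comparisons, each with a true difference of 0.50 SD:

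- Means 1.5 and 1.0: 1.639 − 1.288 = 0.35.
- Means 1.0 and 0.5: 1.288 − 1.009 = 0.28.

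These assume the rule is applied alike in both arms. If it were acted on only in the better arm, the first comparison would give 1.639 − 1.000 = 0.64, larger than the true 0.50. The direction is therefore not fixed.

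**The case against.** The strongest reply is that exclusion in Section 2.12 may mean stopping treatment only. The sentence sits among the intervention rules and does not say excluded from what, while Section 2.15, which governs the analysis, keeps patients in their allocated groups. That reading is possible, so a reader who infers that the plan flatly abandons intention-to-treat goes further than the text. But the article does not state that reading either, and for serious adverse events it speaks of leaving the trial.

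Several other strong readings are tempting and should not be made:

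- That the separate analysis would be empty. Section 2.15 also sends low home compliance and self-withdrawal there, so it would not be.
- That two attendance thresholds conflict. The figure below 50% follows home compliance, whereas Section 2.12 concerns appointments, so no conflict is shown.
- That harm would be hidden. Adverse events are a listed outcome, rated during and after treatment.

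It can also be said that the linear mixed models named in Section 2.15 can keep measurements already taken. They can, although the article's gloss of two-way mixed ANOVA leaves that unclear. A patient excluded during treatment and not measured again would contribute only a baseline value, so the model would not see the worsening.

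Finally, the article condenses a fuller protocol and may be clearer there. The point nevertheless concerns statements that are made here and do not fit together.

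**Conclusion.** The point holds as an unreconciled set of statements. Sections 2.9.2 and 2.12 remove randomised patients on grounds that arise after allocation. Section 2.15 says they are analysed as allocated, and nothing says their outcomes are still collected. Followed literally, the trial could lose primary outcome data on grounds related to adherence and to the outcome itself, which would weaken the claim to internal validity in Section 4.

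The size is not known. The shrinkage of 0.50 SD to 0.35 or 0.28 rests on assumed means, normality, complete removal of worsened patients and equal application of the rule. The 8.6% to 26% range rests on independent misses and on exclusion meaning loss of data; at a 5% miss rate the loss stays inside the 10% allowance. A reader might infer that the bias runs toward no difference. The documents do not support that as a firm statement: Section 2.12 does not say who decides that symptoms have worsened, and Section 3 says the treating therapist cannot be blinded, so equal application is not assured.

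**What to change.** Reconcile Sections 2.9.2, 2.12 and 2.15 by separating the stopping of treatment from leaving follow-up and the analysis set. State that:

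- missed sessions, worsening or an adverse event do not by themselves end outcome collection or remove a patient from the primary analysis;
- NDI and VAS are collected at weeks 4 and 16 from all randomised patients unless they withdraw consent, which respects the right to withdraw in Section 2.6;
- the rule on missed appointments serves only to define the separate (per-protocol) analysis.

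When treatment should stop is a clinical matter for the investigators, and no rule is proposed here.

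The cost is a few sentences of protocol text, communicated to the ethics committee if it counts as an important modification (Section 2.2), and follow-up assessments for a few more patients. Section 2.13 says the trial had not started when the article was written; the change is simplest before the first patient is randomised.
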